### Inclusion and exclusion criteria

The inclusion criteria include a formal clinical diagnosis of ASD and an assessed overall and verbal IQ of 50–84 by a certified clinician. Children who report hypersensitivity to sounds will be included with consent but will be withdrawn immediately if adverse reactions that cannot be controlled (e.g., screaming, attempts at self-harm) are observed. Intervention trainers, assistants, or parents of participants will be encouraged to report any adverse events to facilitate timely response.

Children who exhibit severe physical or sensory disabilities (e.g., deafness) that may limit their participation in either intervention will be excluded. Children with other neurodevelopmental, psychiatric, or neurological comorbidities or are on prescribed psychiatric medication will also be excluded from the study. Children who already engage in music therapy or other social skill interventions (excluding standard care) will be ineligible to enroll in the study.

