## Methods/design

### Study design

The proposed study will be a randomized controlled trial with two parallel groups. Recruited children will first be screened for eligibility and then matched into pairs by age and gender by a research assistant. Another research assistant will assign individuals in each pair to the treatment group (social skill intervention with music) or control group (non-musical social skill intervention) using random number sequences. Participants in the same condition will then be separated into groups of eight by drawing lots. The research assistants performing participant matching and randomization will not be involved in data collection or outcome assessments. The pre-tests and post-tests will include (i) childhood autism rating scale-second edition (CARS-2) rated by an independent rater, (ii) social responsiveness scale-second edition (SRS-2) rated by parents, and (iii) EEG recording. Pre-tests will be administered 2 weeks before intervention, while post-tests will be administered 2 weeks and 4 months after intervention. In each intervention week for 12 weeks, the participants will undergo one 45 min session of social skill training. Within each condition, the same trainer will be responsible for all sessions to minimize differences in intervention delivery across groups. The intervention sessions will be videotaped, and social behavior in the first and last sessions will be coded offline. Figure 1 shows an overview of the study design. Should protocol modifications become necessary, the amendments will be communicated to relevant parties, including research personnel, intervention trainers, participants and their parents, the trial registry, the journal that published the study protocol, and the funding body.

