### Interventions

#### Treatment group intervention

##### Trainers and participants

The treatment group will receive social skill intervention using music therapy in groups of eight. A certified music therapist with prior experience with children with ASD and ID will be the trainer for the treatment group. Parents or primary caregivers will be invited to attend the intervention sessions and to observe the training. An assistant trainer will also be present in all sessions to facilitate the group activities, manage unexpected situations, and ensure the safety of the participants.

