#### Control group intervention

##### Trainers and participants

The control group will receive behavioral-based social skill training in groups of eight. The trainer will be a registered social worker with experience in providing social skill training for children with ASD and ID. Parents or the primary caregivers will be invited to attend the intervention sessions and to observe the training. An assistant trainer will also be present in all sessions to provide support.

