### Assessment of treatment fidelity

Before intervention commences, the intervention manual will be shared with the trainers to facilitate their preparation and delivery of intervention. All materials and procedures that have been developed will be clearly described and explained in pre-intervention meetings with trainers. Adherence to the protocol and trainer competence will be directly assessed by the recorded video data and by independent review of the intervention session notes. The inter-trainer reliability and evaluation of treatment integrity will be reported in the outcomes. Participants will be asked for reasons for discontinuation or deviation from intervention protocols.

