##### In-session social behavior

The intervention sessions in the treatment and control groups will be videotaped using a high-resolution video camera, and data from the first and last sessions will be coded for target social behavior. The three main types of behavior, namely, initiation, turn taking, and eye contact, will be examined using a microanalysis of video recordings in one-second intervals [19]. Target social skills were selected based on the expected types of behavior that may occur during the sessions and that are essential for effective social interactions. The frequency and duration of the social behavior will be recorded with the following coding scheme. Initiation includes touching a person, making a verbal request, giving an object to a person, and other actions to get another’s attention. Turn taking includes responding within an appropriate time either verbally or non-verbally and not interrupting out of turn. Eye contact includes directing the gaze toward the person speaking or acting. The behavior will be further categorized as instructor-to-participant social interactions or participant-to-participant social interactions. Inter-rater reliability will be determined in 20% of coding. These behavioral outcomes are important indices of how much and how appropriately children engage in social interactions. Video data from each session will also be used to indicate the amount of explicit instruction (talking time of the trainer) and amount of music use, to validate the fidelity of the interventions. These data may be included as covariates in data analyses if they are significantly different across groups.

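### The only stated route for collecting adverse events is spontaneous reporting by people who know the arm, with a different trainer in each arm, so events are likely to be under-recorded and harms described by arm could partly reflect who reports

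*Protocol article*

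**What the plan says.** On collecting harms, the protocol article (Inclusion and exclusion criteria) says: "Intervention trainers, assistants, or parents of participants will be encouraged to report any adverse events to facilitate timely response". The same section admits children with reported sound hypersensitivity, with consent, and says that they "will be withdrawn immediately if adverse reactions that cannot be controlled (e.g., screaming, attempts at self-harm) are observed". It does not name the observer.

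On who is in the room, Study design says: "Within each condition, the same trainer will be responsible for all sessions to minimize differences in intervention delivery across groups". For the music arm, "A certified music therapist with prior experience with children with ASD and ID will be the trainer for the treatment group". For the control arm, "The trainer will be a registered social worker with experience in providing social skill training for children with ASD and ID". Both arms also have an assistant trainer at every session. In the music arm that person's duties include dealing with the unexpected and keeping participants safe. In the control arm the duty is described only as support. Parents or caregivers in both arms may come and watch.

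On other records, In-session social behavior states that "data from the first and last sessions will be coded for target social behavior". It adds: "Video data from each session will also be used to indicate the amount of explicit instruction", together with the amount of music used. Assessment of treatment fidelity provides for checking adherence and competence from video and "by independent review of the intervention session notes". It also provides for asking participants why they stopped or deviated. Statistical analyses compares completion between conditions and considers the reasons. No comparison of adverse events between arms is described.

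**The concern.** Encouraging people to report is a stated method, and it is a weak one for this trial. The Background describes children with low verbal ability who may find responses hard to express, so detection depends on adults who watch, judge an episode worth mentioning, and then mention it. Nobody is asked a fixed question, and nobody has to record that a session passed without an event. A session with no report could mean that nothing happened or that nothing was passed on.

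The people best placed to report also know the arm, and the trainer differs completely between arms. If harms are later described by arm, a difference in events cannot be separated from a difference in reporters.

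This matters because the plan itself names screaming and attempts at self-harm as possible reactions. The Background cites an earlier review in which no adverse effects were reported, and the Discussion looks ahead to wider use in schools. A reassuring result from passive reporting would be hard to interpret.

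**Working it through.** The article has no figure on adverse events to reproduce. The check sets its statements side by side.

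**Step 1. Is the route solicited or spontaneous?** The sentence under Inclusion and exclusion criteria encourages three kinds of reporter and gives timely response as the aim. That is spontaneous reporting.

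**Step 2. Do the reporters know the arm, and do they differ by arm?**

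| Reporter | Music arm | Control arm | Knows the arm |
|---|---|---|---|
| Trainer | One music therapist, all sessions | One social worker, all sessions | Yes, delivers the intervention |
| Assistant | Every session; duties include safety | Every session; duty worded as support | Yes, works in the sessions |
| Parent | Invited to observe | Invited to observe | Yes; Primary outcomes says so and warns of expectation bias |

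Trainer and arm coincide completely. The article does not say whether the assistants are different people in the two arms, but their duties are worded differently.

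**Step 3. Do other records close the gap?**
- Reasons for stopping are solicited, but only from children who stop or deviate.
- Withdrawal on an observed reaction is stated only for sound-sensitive children whose reaction cannot be controlled.
- Behavioural coding of the first and last sessions covers initiation, turn taking and eye contact.
- Video from each session serves trainer talking time and music use.
- The session-note review is stated for adherence and trainer competence.

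Each could bring a harm to light. None is described as a means of collecting harms.

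**Step 4. What could follow?** Expected reported children per arm = n × true proportion affected × proportion reported. Here n = 40 (Abstract, Method). The other two inputs are assumptions, because the article gives neither.

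| True proportion, both arms | Truly affected per arm | Reported at 0.9 | Reported at 0.5 | Ratio |
|---|---|---|---|---|
| 10% | 40 × 0.10 = 4 | 3.6 | 2.0 | 1.8 |
| 20% | 40 × 0.20 = 8 | 7.2 | 4.0 | 1.8 |
| 30% | 40 × 0.30 = 12 | 10.8 | 6.0 | 1.8 |

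The ratio is simply 0.9 / 0.5 = 1.8, or 0.5 / 0.9 = 0.56 with the arms reversed. If both arms report at 0.5, the 20% case gives 4.0 and 4.0: half the events are lost, but no false difference appears. Under-recording therefore needs reporting below 100%. A false difference needs reporting that differs between arms.

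**The case against.** The strongest reply is that the text offers more protection than one sentence suggests. Trainers, assistants and parents are named on equal terms, an assistant attends every session in both arms, reasons for discontinuation are asked for, and session notes are independently reviewed. The reports are meant to prompt a response, and no between-arm test of harms is stated. This is also a condensed article that refers to a separate full protocol, so forms, definitions and grading may exist elsewhere.

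Much of that stands, and it rules out several stronger readings.

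- A reader might infer that each arm's count rests mainly on its one trainer. The document does not say so, and two other kinds of reporter may be in the room.
- A reader might take the coding of 2 of 12 sessions to mean that 10 of 12, or 83%, go unchecked for harms. That split describes coding of social behaviour. The coded sessions have no stated harms item either, so it does not measure harms coverage.
- A reader might conclude that harms will certainly be under-counted and that any difference between arms is confounded. Both are risks of unknown size. The ratios above rest on assumed reporting rates, and parents are not tied to one trainer's habits.
- A reader might say that the plan expects uncontrolled reactions. Its wording is conditional.

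The reply does not remove the stated method. The criticism concerns the wording the article chose, not the absence of a form. Even without a formal test, any account of harms by arm would carry the reporters' differences with it.

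**Conclusion.** The point holds in a limited form. The stated collection route is spontaneous reporting by unblinded people, trainers differ completely by arm, and the assistants' safety role is written unequally. Under-recording is likely, and a descriptive difference in harms between arms could partly reflect who reports.

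No size can be derived from the document. The 7.2 against 4.0 example shows the mechanism and is not an estimate: it assumes 20% of children affected in both arms and reporting of 90% against 50%. With equal reporting there would be under-recording but no false contrast.

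The efficacy analyses described in the article do not use adverse-event reports, so the weakness bears on what the trial can say about harms.

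**What to change.** Replace the wording that encourages reports with solicited recording that is identical in both arms:

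- On the existing session note, add a mandatory yes/no entry for each child at each session, in which none is an explicit answer. With groups of eight this is eight entries per note, or 40 × 12 = 480 per arm.
- Include these entries in the independent review of session notes already planned under Assessment of treatment fidelity.
- Give the assistants in both arms the same recording duty, in the same words.
- Report harms per child by arm descriptively, with spontaneous parent reports as a supplement.

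This changes recording only. It leaves the handling of reactions and withdrawal as the protocol has it.

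Checking every child on all session video is not part of this proposal. With 80 / 8 = 10 groups, 12 sessions and 45 minutes each, that is 10 × 12 × 45 = 5,400 minutes, or 90 hours. It would be a new task, unlike the planned measurement of talking time and music use.

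The cost is a few minutes per session and possibly a higher, less favourable adverse-event count. Unblinded staff would still make the entries, so differences between reporters would be reduced but not removed.

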### Sample size calculation

The sample size was calculated based on the predicted effect size of 0.71 in generalized social interaction outside intervention context from a meta-analysis of social skill intervention studies using music therapy for children with ASD (aged 2–12) relative to non-music intervention or standard care controls [7]. For a two-group *t* statistics with α = 0.05, power = 0.8, and attrition rate = 25%, a minimum number of 33 participants in each group will likely yield statistically meaningful differences. Given that neural measures can detect autonomic responses and behavioral intentions in addition to explicit actions, they can be considered more change sensitive than behavioral observations. Hence, we expect that recruiting 40 participants in each group will allow us to detect presence of effects in qEEG measures.

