**Method:**

A randomized controlled trial (RCT) with two parallel groups of 40 children each (1:1 allocation ratio) is planned. Participants will receive 45 min of music therapy or non-musical intervention targeting social skills once a week for 12 weeks. Primary outcome measures will be independent ratings on the Childhood Autism Rating Scale and parent ratings on the Social Responsiveness Scale-2. Linear mixed-effects models for these two outcome measures will be created for data collected at 2-week pre-intervention, 2-week post-intervention, and 4-month post-intervention sessions. In-session behaviors at the first and last intervention will be videotaped and coded offline and compared. Pretreatment neural response of quantitative electroencephalograms (qEEG) to social scenes will be used to predict the outcomes of musical and non-musical social skill interventions, whereas qEEG responses to music will be used to predict the effectiveness of musical social skill intervention.

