### Objectives

Aims and hypotheses to be tested:
On the group level, is social skill intervention using music therapy more effective in enhancing social interaction than non-musical social skill training for children with ASD and co-occurring mild/borderline ID?On the individual level, are participants with enhanced left-lateralized FAA to social scenes relative to baseline more responsive to both types of social skill interventions?For participants in the music therapy intervention, does enhanced left-lateralized FAA to preferred music relative to baseline predict better outcomes in social skill development?

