### Outcome measures

#### Primary outcomes

The primary outcome measure is autistic severity as assessed using a standardized rating scale by an independent rater who will be blinded to the study group allocation. This outcome was selected because observing behavioral changes that generalize to other social contexts outside of the intervention is the ultimate goal of social skill intervention. Parental rating by using a standardized rating scale is included as another outcome to support the clinical assessment. Parents are good informants because they spend time with the participants outside of intervention contexts, but they are not blinded to the group assignment and may exhibit expectation biases. Another outcome is the behavioral changes at the last intervention sessions relative to the first session. Trained research assistants who are blinded to the session number and study hypotheses will code for target social behaviors by using video data. This measurement will provide an objective measure of the social skills exhibited by participants within the intervention setting.

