##### CARS-2

The general autistic symptoms of the participants will be assessed using CARS-2 [15], by a qualified and experienced assessor. This scale consists of 15 questions rating the autistic symptoms and general impression of deviance based on behavioral observations. Each question is rated from 1 to 4, and high scores are associated with a high level of impairment. Scores below 30 indicate that an individual does not have ASD, scores between 30 and 36.5 imply mild to moderate autism, and scores from 37 to 60 correspond to severe autism. The psychometrics of CARS-2 is well documented in Western and Chinese contexts [15, 16].

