##### SRS-2

Parental ratings of generalized social interaction outcomes will be collected using SRS-2. A parent of each participant will be asked to complete the SRS-2 based on their observations of their child over the previous 3 months. The scale is a 65-item questionnaire that measures the severity of social impairments associated with ASD [17]. The five subscales include social awareness, social cognition, social motivation, social communication, and autistic mannerisms. Each item is rated on a scale from “0” (never true) to “3” (almost always true), and high scores indicate severe social impairments. SRS-2 exhibits good psychometric properties in Western and Chinese contexts and is sensitive to changes in social functioning among children with ASD [17, 18].

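### The only effect size behind the sample size (0.71) is for generalized social interaction; the blinded CARS-2 total, named in Methods as the primary outcome, has no stated effect size, so the 80% power is not shown for it

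*Protocol article*

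**What the plan says.** - **Objectives.** The group-level aim asks: "is social skill intervention using music therapy more effective in enhancing social interaction than non-musical social skill training".
- **Sample size calculation.** The input is a "predicted effect size of 0.71 in generalized social interaction outside intervention context", taken from a meta-analysis, with "α = 0.05, power = 0.8, and attrition rate = 25" per cent, in a two-group t test. The result is that "a minimum number of 33 participants in each group will likely yield statistically meaningful differences". Recruitment is then raised to 40 per group, and the reason given is detection of effects on the qEEG measures.
- **Primary outcomes (Methods).** In the singular: "The primary outcome measure is autistic severity as assessed using a standardized rating scale by an independent rater". The rater is blinded. The choice is explained by the wish to see change that carries over to settings outside the sessions. The parent rating is described as a further outcome that supports the clinical assessment, and the text warns that parents are unblinded and may be biased by expectation.
- **CARS-2.** "The general autistic symptoms of the participants will be assessed using CARS-2", on 15 questions.
- **SRS-2.** "Parental ratings of generalized social interaction outcomes will be collected using SRS-2". This subsection sits under the Primary outcomes heading.
- **Abstract, Method.** CARS and SRS-2 are named together as the primary outcome measures.

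**The concern.** A power statement belongs to one outcome and one assumed effect on it. Here the effect is described in almost the same terms as SRS-2, while the Methods text gives the primary role to a general severity scale. Nothing in the article gives an effect size or standard deviation for CARS-2, or explains why 0.71 should hold for it.

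Two things are at stake. The first is the stated power: a reader will take the 80% as applying to the blinded primary outcome, and that has not been shown. The second is interpretation. A CARS-2 result, positive or null, is a statement about autistic severity and does not by itself answer Aim 1. If the unblinded SRS-2 were positive and the blinded CARS-2 null, the plan gives no basis for telling parental expectation from low power on CARS-2.

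**Working it through.** **Inputs from the protocol.** d = 0.71, α = 0.05, power 0.80, attrition 25%, two-group t test, stated minimum 33 per group (Sample size calculation); 40 per group planned (Abstract, Method). The number of sides is not stated; two-sided is assumed below.

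**Formula.** With n evaluable per group, power = P(|T| > t(0.975; 2n − 2)), where T is noncentral t with 2n − 2 degrees of freedom and noncentrality d√(n/2).

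**Step 1: reproduce the plan's figure.** For d = 0.71 and n = 33, the noncentrality is 0.71 × √16.5 = 2.88 and power is 81.1%. This is the smallest n that reaches 80%, so 33 reproduces as a number of evaluable children. The normal approximation, 2 × ((1.960 + 0.842)/0.71)² = 31.1, rounds up to 32.

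The 33 does not contain the 25% attrition under a two-sided test, since 33/0.75 = 44. A one-sided t test needs 26, and 26 × 1.25 = 32.5 also rounds up to 33, so the derivation of the figure is not certain. That is a separate matter. It is used here only to fix the two evaluable sizes: 40 if nobody is lost, and 40 × 0.75 = 30 if a quarter are.

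**Step 2: match outcome to effect size.**

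| Item | Construct in the protocol's terms | Effect size given |
|---|---|---|
| Aim 1 | social interaction | – |
| Sample size | generalized social interaction | 0.71 |
| SRS-2 (parent, unblinded) | generalized social interaction | same label as the 0.71 |
| CARS-2 (independent rater, blinded) | general autistic symptoms, autistic severity | none |

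**Step 3: power for CARS-2 over an assumed range.** The documents give no CARS-2 effect, so the values of d below 0.71 are assumptions.

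| d on CARS-2 | Power, 40 per group | Power, 30 per group | Evaluable n per group for 80% (recruited, with 25% loss) |
|---|---|---|---|
| 0.71 | 88% | 77% | 33 (44) |
| 0.6 | 76% | 63% | 45 (60) |
| 0.5 | 60% | 48% | 64 (86) |
| 0.4 | 42% | 33% | 100 (134) |

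The smallest effect detectable with 80% power is 0.63 with 40 evaluable per group and 0.74 with 30. The planned trial therefore has 80% power on CARS-2 only if the effect there is close to the one assumed for social interaction.

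**The case against.** The strongest reply is that the plan is consistent where it matters. The 0.71 matches Aim 1. The Abstract and the section heading make SRS-2 primary as well, so one named primary outcome does correspond to the powered construct. The Methods text also gives a reason for the severity rating, generalization beyond the sessions, which echoes the description of the effect size, and the Background defines autism partly by deficits in social interaction. All of this stands, and it limits the point to CARS-2. It does not supply a CARS-2 effect size. A reason for choosing an out-of-session rating is not a reason to expect 0.71 on a general severity total.

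Several stronger readings are tempting but not supported:

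- *The stated power does not match the aim.* It does; only CARS-2 departs from both.
- *CARS-2 is the sole deciding measure.* The Abstract says otherwise.
- *The 0.71 was not estimated on anything like CARS-2.* The documents do not say which instruments the meta-analysis pooled. The match to SRS-2 is one of labels.
- *CARS-2 power is known to be very low because only its social items can move.* If 10 of 15 equally variable items respond with a joint shift of 0.71, the rest do not change and the inter-item correlation is 0.2 to 0.5, the total shifts by 0.48 to 0.50; with 5 items, by 0.25 to 0.28. The protocol gives no item list, and the assumption of no change elsewhere produces the whole loss. These figures are illustrative only.

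It is also fair to say that the planned analysis is a mixed model with repeated measures, covariates and random group effects, so the t-test figures are not the power of that model. They are on the same footing as the protocol's own calculation.

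**Conclusion.** The point holds for CARS-2 only. The sample size section supports 80% power for a generalized social interaction outcome, which in this trial is SRS-2 by the protocol's own description. It does not show that power for the blinded CARS-2 total, which the Methods text names as the single primary outcome. The Abstract and Methods also differ on whether SRS-2 is primary or supportive, so a reader cannot tell whether the powered outcome is a deciding one.

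The size cannot be fixed from the documents. Under assumed CARS-2 effects of 0.6 to 0.4, power is 76% to 42% with 40 evaluable per group and 63% to 33% with 30, against 88% and 77% at 0.71. These figures assume a two-sided 5% t test at one time point, without covariates or clustering.

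This should be corrected because it changes a stated figure and what may be concluded. It is not a flaw in the randomized comparison, and it does not show that CARS-2 is a wrong choice.

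**What to change.** 1. In the sample size section, state that the 0.71 and its power refer to a generalized social interaction outcome, SRS-2 in this trial. For CARS-2, either give power separately over an openly assumed range, such as the table above, or justify why 0.71 should hold for it.
2. Make the Abstract and the Primary outcomes text agree on whether SRS-2 is co-primary or supportive.
3. Word conclusions from the CARS-2 total as autistic severity, and do not read a null CARS-2 total alone as showing no effect on social interaction.

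The cost is a few sentences and a less favourable stated power for CARS-2. No new data are needed. A new CARS-2 score limited to social items is not required: the protocol mentions no such score, and it would have less published psychometric support than the total.

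### The minimum of 33 per group lists 25% attrition among its inputs, but on a two-sided test 33 is the evaluable number before any attrition

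*Protocol article*

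**What the plan says.** The Sample size calculation section of the protocol article starts from a "predicted effect size of 0.71 in generalized social interaction outside intervention context", drawn from a meta-analysis of music therapy studies. It names a two-group t statistic at α = 0.05 and gives the result: "power = 0.8, and attrition rate = 25%, a minimum number of 33 participants in each group will likely yield statistically meaningful differences". It does not say whether the test is one-sided or two-sided, or whether 33 counts children recruited or children completing.

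The same section then raises the number to 40 per group, on the ground that neural measures should be more sensitive to change than behavioural observation: "we expect that recruiting 40 participants in each group will allow us to detect presence of effects in qEEG measures". Attrition plays no part in that step, and no power is given for 40 per group. The Abstract confirms 40 per group at 1:1, and the Participants section confirms 80 in total.

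**The concern.** Attrition is listed beside power and α as an input to the 33, so a reader takes 33 as the number to recruit, with the loss of a quarter of the children already covered. A standard two-sided calculation returns 33 with no loss at all. If that is how the figure arose, the attrition allowance was named but never applied, and the minimum is 11 per group too low (44 − 33).

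The paragraph is the protocol's only statement of power, and it would be used to judge whether a non-significant result is informative. The later step to 40 does not repair it, because that step is argued from the sensitivity of qEEG.

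**Working it through.** **Inputs.** All come from the Sample size calculation section: d = 0.71 (standardised, so SD = 1), α = 0.05, power 0.80, attrition 25%, stated minimum 33, planned recruitment 40 per group. Allocation is 1:1 (Abstract). Sidedness is not stated, so both cases are computed. Loss is assumed equal in the two arms.

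**Formulas.** Power comes from the noncentral t distribution with n evaluable per group, 2n − 2 degrees of freedom and noncentrality d√(n/2). Recruitment allowing for loss is n/(1 − 0.25). The normal approximation, n = 2((z_α + z_power)/d)², serves as a check.

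**Step 1: reproduce 33, two-sided.** The t test requires n = 32.13, which rounds up to 33. Power is 0.798 at n = 32 and 0.811 at n = 33. The normal approximation gives 31.14, so 32. The printed 33 is matched exactly, with no attrition in the calculation.

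**Step 2: apply 25% attrition, two-sided.** 33/0.75 = 44 per group, or 88 in total (normal approximation: 32/0.75 = 42.7, so 43). Multiplying by 1.25, which is the wrong adjustment, gives 33 × 1.25 = 41.25, so 42 (normal approximation: 32 × 1.25 = 40). No two-sided version that includes attrition gives 33.

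**Step 3: try a one-sided test.** The t test requires 25.23, so 26 evaluable. Dividing by 0.75 gives 34.7, so 35 recruited. Multiplying by 1.25 gives 32.5, so 33. The normal approximation gives 24.53, so 25 evaluable and 34 recruited. An attrition-inclusive figure at or near 33 is therefore possible, but only with a one-sided test.

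**Step 4: power after 25% loss, by t test.**

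| Recruited per group | Evaluable per group | Two-sided power | One-sided power |
|---|---|---|---|
| 33 | 33 × 0.75 = 24.75 (24 to 25) | 0.67 to 0.69 | 0.78 to 0.80 |
| 40 | 40 × 0.75 = 30 | 0.77 | 0.86 |
| 44 | 44 × 0.75 = 33 | 0.81 | 0.89 |

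The effect detectable with 80% power, two-sided, is 0.81 at 25 evaluable, 0.74 at 30 and 0.70 at 33. By the normal approximation, two-sided power at 30 evaluable is 0.785.

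**The case against.** The strongest reply is that the two-sided test is the reviewer's assumption. The first aim is worded directionally, asking "is social skill intervention using music therapy more effective in enhancing social interaction than non-musical social skill training", and nothing in the article rules out a one-sided test. On that reading 33 recruited has power of 0.78 to 0.80 after attrition, and 40 recruited has 0.86. This stands, and it limits the finding. It does not remove it: a directional aim does not declare a one-sided test, a bare α of 0.05 is conventionally read as two-sided, and even one-sided the t test asks for 35 rather than 33.

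A second reply is that nobody plans to recruit 33. The trial will recruit 40, and the protocol attaches no 80% claim to that number. This also stands. The two-sided gap at 40 is small: 2.8 points by t test (0.800 − 0.772) and 1.5 by the normal approximation (0.800 − 0.785). That is little beside the uncertainty in the assumed effect. One could also suppose that 40 already carries the attrition, since 32 × 1.25 = 40. The protocol does not say so, and adding 25% does not offset losing 25%, since 40 × 0.75 = 30.

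A third reply is that a t test in completers is not the planned analysis. The Statistical analyses section specifies mixed models with pre- and post-intervention data and covariates, which could raise power. As an illustration, with an assumed baseline correlation of 0.30 and a variance factor of 1 − r², 30 completers are worth 30/0.91 = 33. Delivery in groups of eight works the other way. With six completers per group and assumed intraclass correlations of 0.01, 0.05 and 0.10, the design effects 1 + 5 × ICC are 1.05, 1.25 and 1.50, and two-sided power at 30 falls to 0.75, 0.67 and 0.59. The protocol gives neither correlation, so the power of the planned analysis cannot be settled here. The finding concerns only the calculation as stated.

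**Conclusion.** The sample size statement needs correction. Under a two-sided t test, 33 per group is the evaluable number before attrition, and listing 25% attrition among its inputs is wrong. The matching recruitment figure is 44. Recruiting 33 would give power of about 0.69, and the planned 40 gives about 0.77 with a detectable effect of about 0.74. These figures assume a two-sided α of 0.05, equal loss in both arms, and a simple comparison of completers.

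A reader might infer that the planned 40 per group misses 80% power under the plan's own assumptions. The documents do not support that. The shortfall at 40 depends on a two-sided test that they never state, it disappears one-sided, and they claim no power for 40. Nor can it be said that 33 arises only from a one-sided number wrongly multiplied by 1.25: it is also exactly the two-sided number with attrition left out, and a one-sided number divided correctly by 0.75 comes to 34 or 35. What holds is that no two-sided calculation including attrition gives 33, and that the step to 40 is not argued from attrition.

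**What to change.** In the Sample size calculation section, state whether the test is one-sided or two-sided, and whether each number counts children recruited or children evaluable.

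- If two-sided: give 33 evaluable per group, equivalent to 44 recruited at 25% loss, for 80% power at an effect of 0.71. Report that the planned 40 per group leaves about 30 evaluable, with power of about 0.77 and a detectable effect of about 0.74.
- If one-sided: declare it, give 26 evaluable and 35 recruited, and report about 0.86 for 40 recruited.

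In either case, say that the figure is for a simple t test, before any loss from clustering in groups of eight and any gain from baseline and repeated measures in the mixed model. Keep the qEEG argument separate from the attrition allowance.

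The cost is a few sentences. No added recruitment is needed to correct the statement. The only downside, if the test is two-sided, is a stated power slightly below 0.80.
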